## Abbreviations, Acronyms and Definitions

|       |                                       |
|-------|---------------------------------------|
| BPA:  | Best Practice Advisory                |
| CDS:  | Clinical Decision Support             |
| CT:   | Computed tomography                   |
| ED:   | Emergency Department                  |
| EHR:  | Electronic Health Record              |
| FAQ:  | Frequently Asked Questions            |
| HP:   | HealthPartners                        |
| ICU:  | Intensive Care Unit                   |
| IRB:  | Institutional Review Board            |
| KPNC: | Kaiser Permanente Northern California |
| MOO:  | Manual of Operations                  |
| N/A:  | Not applicable                        |
| OR:   | Operating Room                        |
| PI:   | Principal Investigator                |
| RA:   | Research Assistant                    |
| US:   | Ultrasound                            |

## 1) Summary

Abdominal pain is one of the most common reasons for children and adolescents to seek care in the emergency department (ED). Computed tomography (CT) has been promoted as a method to improve diagnostic accuracy when evaluating patients with acute abdominal pain. In the past 20 years, CT use has increased dramatically, especially for children receiving care in general ED settings. Although in some adult cohorts, increased CT use has been associated with decreased rates of negative appendectomies, similar improvements in health outcomes among children with acute abdominal pain have not occurred. Negative consequences of CT include increased costs and substantial exposure to ionizing radiation.

Although appendicitis is the most common surgical emergency in children, its diagnosis remains a challenge and thus, emergency department (ED) providers increasingly rely on computed tomography to distinguish appendicitis from other conditions. This project (a) uses electronic health record (EHR) technology to deliver patient-specific clinical decision support to ED providers at the point of care, (b) assesses the impact of this intervention on the use of diagnostic imaging and clinical outcomes, and (c) assesses the impact of the intervention on the costs of care delivered.

Appy CDS is an automated, evidence-based tool designed to provide point-of-care clinical decision support (CDS) to providers for pediatric patients presenting to the emergency department (ED) with acute abdominal pain. Appy CDS uses Epic and web-based algorithms to provide recommendations, consistent with standard of care and informed by a personalized appendicitis risk calculation. The Appy CDS will be implemented and evaluated within two large health systems, HealthPartners (HP) and Kaiser Permanente Northern California (KPNC). The overall approach and algorithms driving the appendicitis risk calculation within Appy CDS will be the same at the KPNC and HP sites. However, the actual implementation and appearance of the CDS may vary, based on local differences between the two health systems in: workflow, current EHR structure, and preferences of clinical leaders.

If successful, this flexible decision support tool could be adapted and implemented broadly in a range of acute care settings to both standardize and personalize care delivered to pediatric patients.

## 2) Introduction

### a) Background

Acute abdominal pain is the chief complaint for 5%-10% of all emergency department (ED) visits among children. Up to 10% of these patients have appendicitis, the most common surgical emergency in this age group. Due to overlap in presentation between appendicitis and nonsurgical conditions, identifying the etiology of acute abdominal pain can be difficult. Thus, ED providers increasingly use computed tomography (CT) to diagnose appendicitis. From 1998-2008, in a national sample of pediatric ED visits, CT use among children with abdominal pain increased from 0.9% to 15.4%. Furthermore, children receiving care at general EDs were more likely than those at pediatric EDs to undergo CT. In fact, general facilities are both the predominant providers of emergent care in the United States and the major source of ionizing radiation exposure in children. CT use in children is associated with increased costs and adverse health effects without consistent clinical benefits.

Previously, our group and others have developed and validated clinical decision rules for children with acute abdominal pain. Goals of these rules have been to identify: 1) patients at high risk for appendicitis who do not require imaging before surgery; and 2) patients at low risk for appendicitis, for whom the risks of CT may outweigh the benefits. In our pilot study, we demonstrated that providing ED clinicians a child's estimated risk for appendicitis based on their current symptoms can reduce CT use. The current proposal expands on our prior formative work by creating an electronic health record (EHR)-linked, web-based clinical decision support (CDS) system that integrates data from multiple sources and presents point-of-care CDS in order to augment clinician judgment and prioritize care delivery. Such a CDS system is likely to be an efficient and scalable method for translating evidence into practice across multiple general EDs, the primary sites where children with acute abdominal pain receive emergent care.

Community-based EDs in two regions will develop, implement, and prospectively evaluate a web-based CDS tool (Appy-CDS) for children with acute abdominal pain. Appy-CDS will identify pediatric patients with acute abdominal pain at increased risk for appendicitis, notify providers of a patient's estimated risk for appendicitis, and provide specific evidence-based recommendations. To measure the impact of Appy-CDS, we will conduct a cluster- randomized trial across 17 participating EDs in two large health systems with a combined total of more than 90,000 pediatric visits per year.

Specific Aim 1: To design and implement a triage-based trigger, as part of Appy-CDS, to identify pediatric patients with acute abdominal pain at increased risk for appendicitis.

- Hypothesis 1: Among pediatric patients with abdominal pain, a triage-based trigger will identify those at risk for appendicitis with a negative predictive value  $\geq 99\%$  and positive predictive value  $\geq 20\%$ .

Specific Aim 2: To evaluate the impact of the full Appy-CDS intervention on appropriate use of diagnostic imaging (CT and ultrasound) for pediatric patients with acute abdominal pain at risk for appendicitis.

- Hypothesis 2. Among eligible pediatric patients at risk for appendicitis, those treated at intervention EDs compared to those treated at control EDs will be less likely to undergo a CT examination.

- Hypothesis 3. Among eligible pediatric patients at risk for appendicitis, those treated at intervention EDs compared to those treated at control EDs will be less likely to undergo diagnostic imaging with CT or ultrasound.

**Specific Aim 3:** To evaluate the impact of the full Appy-CDS intervention on health care costs.

- Hypothesis 4. Among pediatric patients at risk for appendicitis, those treated at intervention EDs compared to those treated at control EDs will have significantly lower resource use in a defined 7-day period after an index ED visit.

In addition, we will monitor rates of appendiceal perforation, negative appendectomies, and missed appendicitis in our study cohort to ensure the safety of our proposed intervention. This innovative project builds on extensive previous work by our interdisciplinary team, including derivation and validation of pediatric ED clinical decision rules, CDS development and implementation, and economic and statistical analyses of ED resource use. The proposed point-of-care CDS tool will be a scalable model for using EHR-linked, web-based technology to safely deliver personalized and evidence-based care for children in the ED.

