Complete data for the validation of pARC were available for 1426 patients. Across seven clinically actionable risk categories (< 5%, 5-14%, 15-24%, 25-49%, 50-74%, 75-84% and ≥ 85%) the pARC score provided valid risk prediction. The AUC for pARC was 0.85 (95% CI 0.83-0.87).

**Hypothesis 1:** Among pediatric patients with abdominal pain, a triage-based trigger will identify those at risk for appendicitis with a negative predictive value ≥99% and positive predictive value ≥20%.

The purpose of the *Triage CDS* (triage-based trigger) is to reliably identify a study cohort at elevated risk of appendicitis at both the intervention and control EDs. This cohort will comprise the analytic sample used to determine the impact of the Appy-CDS system on our key outcomes of CT and ultrasound use (Hy 2 & 3) and health care costs (Hy 4). In addition, data from *Triage CDS* will be included in the appendicitis risk algorithm (as detailed above). Final content of *Triage CDS* will be based on our previous decision rule, expert opinion, and review of ED workflow; Appendix A demonstrates the questions that are included.

Assessment of the *Triage CDS* will consist of 2 steps. First, the frequency that triage nurses or providers answer questions when prompted in the EHR (pain duration <96 hours, pain on right side, history of emesis, pain with walking) will be identified. Second, among pediatric patients with complete data in the EHR, the negative and positive predictive value of the triage tool will be determined. We hypothesize that among pediatric patients with complete data, the triage tool will yield a positive

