predictive value of at least 20% and a negative predictive value of at least 99%. Due to variation in design, patient load, and number of urgent pediatric presentations, we anticipate considerable differences in data capture across EDs. Identifying these differences will inform optimal site-specific system design and training. If the positive or negative predictive value deviates substantially from our goals, (i.e., a 95% confidence interval for negative predictive value failing to include 99%), before full implementation we will review EHR data for all appendicitis cases and refine our trigger. Following implementation, we will prospectively track the performance of the *Triage CDS* at each site and report performance metrics (sensitivity, specificity, positive predictive value, and negative predictive value). If significant differences are discovered across study sites, we will use site-specific estimates of negative and positive predictive values as covariates in multivariate analysis of our key study outcomes (Hy 2-4).

**Hypotheses 2 and 3:** Appy-CDS implementation will reduce CT and total diagnostic imaging (CT and ultrasound) in patients identified as at risk for appendicitis.

Effectiveness of the full Appy-CDS system will be evaluated using a cluster-randomized trial. We will include data from both the pre and post intervention periods in the analysis to account for site-specific variation and potential imbalances in baseline imaging use. Our analysis will follow an intent-to-treat approach and consider both randomization and the timing of the Appy-CDS implementation at the particular study site. Patient and ED- level confounding will be addressed in three ways. First, our paired randomization scheme will attempt to balance potential confounders across study arms before Appy-CDS implementation. Second, we will use a pre- post intervention design to account for imbalances at baseline in imaging use. Third, before final analysis, we will compare patient characteristics across study arms and randomized pairs. If ED or patient-level characteristics deviate in the control and intervention arms, they will be adjusted for in multivariable models.

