### Enrollment reporting, by Cluster and health system

\*Column A: Starting with cc of abdominal pain and excluding; left prior to being seen, had prior ED visit, trauma, pregnant, chronic condition/medication, or prior appendectomy, and for HP only BPA did not fire

\*\*Column B: Screening questions not completed includes 1) nurse not completing BPA questions at HP, provider not completing questions via BPA or CDS at HP, provider not accessing RISTRA at KP.

\*\*\*Column C: Screening questions; is abdominal pain diffuse, is there right sided abdominal pain, pain for 5 days or less

|                            |         | Column A*                       | Column B**                              | Column C***                                 | Column D       | Column E                                               |
|----------------------------|---------|---------------------------------|-----------------------------------------|---------------------------------------------|----------------|--------------------------------------------------------|
| Label                      | Site(s) | Potential eligible patients (n) | Screening questions not completed n (%) | Excluded based on screening questions n (%) | ENROLLED n (%) | # months in study (starting with intervention go live) |
| HP Cluster 1 intervention  |         |                                 |                                         |                                             |                |                                                        |
| HP Cluster 1, control      |         |                                 |                                         |                                             |                |                                                        |
| HP Cluster 2, intervention |         |                                 |                                         |                                             |                |                                                        |
| HP Cluster 2, control      |         |                                 |                                         |                                             |                |                                                        |
| KP Cluster 1, intervention |         |                                 |                                         |                                             |                |                                                        |

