We will compare ED visits for the target age group with abdominal pain as a chief complaint to confirm either cohort entry or intentional exclusion. Those who appear to be eligible but not included in the cohort will be listed as missed eligible. On a quarterly basis we will review missed eligible cases and review for cases of appendicitis in this group.

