## Provider selects or enters reason for not completing triage questions.

Research (1 Advisory)

Based on chief complaint, patient is eligible for the Pediatric Abdominal Pain study. After you examine the patient, click the blue hyperlink below to complete up to 3 questions. If appendicitis is not part of your differential diagnosis, please select an acknowledgment reason.

Acknowledge reason:

Epigastric or left sided pain | Chronic abdominal pain | Previous appendectomy | Other reasons (add comments)

Go to Abdominal Pain Additional Assessment Questions.

Refresh Last refreshed on 9/29/2016 at 12:02 PM Accept

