## Appendix B: Intervention Design and Workflow- KP

### a) Capturing eligibility: RISTRA

The analogous triage alert at KPNC will be implemented using the RISTRA interface existing at KPNC. For patients with a chief complaint of abdominal pain, ED providers will be trained to click on the RISTRA icon embedded within the EHR.

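### Hypothesis 1 is worded for all pediatric patients with abdominal pain but tested only in visits with complete screening data, so it could be declared met for a wider population than was examined

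*Combined protocol and SAP*

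**What the plan says.** Section 2a (Specific Aim 1) states Hypothesis 1 without any completeness condition: "Among pediatric patients with abdominal pain, a triage-based trigger will identify those at risk for appendicitis with a negative predictive value" of at least 99% and a PPV of at least 20%. The Hypothesis 1 heading in section 6a repeats it.

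Section 6a evaluates the trigger in two steps. Step 1 counts how often staff answer the prompted questions; no target is set. In step 2, "among pediatric patients with complete data in the EHR, the negative and positive predictive value of the triage tool will be determined". The goals are restated for complete-data patients: a positive "predictive value of at least 20% and a negative predictive value of at least 99"%. The trigger is to be refined before full implementation if the results deviate substantially, for example "a 95% confidence interval for negative predictive value failing to include 99"%. After implementation, sensitivity, specificity, PPV and NPV are promised for each site, with no denominator named.

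On who answers:

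- **HealthPartners (HP).** If the nurse does not respond, a provider alert follows: "If appendicitis is not part of your differential diagnosis, please select an acknowledgment reason" (Appendix A, Workflow).
- **Kaiser Permanente Northern California (KPNC).** "ED providers will be trained to click on the RISTRA icon embedded within the EHR" (Appendix B, section a).
- **Enrollment report (section 7b), Column B.** "Screening questions not completed includes 1) nurse not completing BPA questions at HP, provider not completing questions via BPA or CDS at HP", and at KPNC the provider not opening RISTRA.

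Section 9, after Table 7, says that eligibility cannot be confirmed when the HP triage alert is not completed, and lists such visits among the missed eligibles. It adds: "On a quarterly basis we will review missed eligible cases and review for cases of appendicitis in this group". No section carries those cases into NPV or sensitivity. The multiple imputation under Missing data concerns patients already identified as at risk.

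**The concern.** An unanswered visit is, in operation, a visit that the trigger did not flag. Any appendicitis in it is a case the trigger failed to identify, yet it is left out of the NPV and of any sensitivity computed on complete data. The omission works in favour of success.

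The unanswered visits are unlikely to be a random subset. The HP fallback alert offers a route around the questions when appendicitis is not suspected, and at KPNC screening starts only when a provider opens the tool. In the example enrollment table (Table 7), KPNC supplies 853 + 767 = 1,620 of 1,899 pre-intervention patients (85%). If providers answer more often when they suspect appendicitis, PPV in answered visits rises through clinician selection rather than through the trigger.

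At stake is what Aim 1 may conclude. The rule for refining the trigger runs on the same complete-data NPV, so a trigger that leaves many appendicitis cases unflagged in use could pass without refinement.

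**Working it through.** **The plan's own figures.** Under Sample size and power, 2,634 / 24,603 = 10.7% have appendicitis (stated as 11%) and about 50% are flagged. Half of 24,603 over 3 years is 4,100 per year, close to the stated 4,200, and 4,200 / 14 = 300 per ED. If every visit were screened with NPV 99%, missed cases would be 0.01 × 50% = 0.5% of visits and PPV = (10.7% − 0.5%) / 50% = 20.4%. The two goals fit the planning figures when every visit is screened.

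**Completion at the example site (Appendix C, site 101, six months).**

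- Not completed: 37 + 10 + 15 + 23 + 18 + 27 = 130
- Screened out: 10 + 14 + 21 + 14 + 12 + 12 = 83
- Enrolled: 17 + 19 + 18 + 16 + 15 + 16 = 101
- Answered: 184 / 314 = 58.6% (by month, 42% to 77%)
- Flagged among answered: 101 / 184 = 54.9%

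**Assumptions, since no document gives the appendicitis rate in unanswered visits.** Overall appendicitis is p = 10.7%, so 314 × p = 33.6 cases. NPV in answered visits is exactly 99%, so 0.83 cases are missed among the 83 screened out. Answered visits have r times the appendicitis rate q of unanswered visits.

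**Formulas.**

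- q = p / (0.586r + 0.414)
- PPV in answered visits = (33.6 − 130q − 0.83) / 101
- NPV over all visits = 1 − (130q + 0.83) / 213, because 83 + 130 = 213 visits are not flagged
- Sensitivity over all visits = (33.6 − 130q − 0.83) / 33.6

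At r = 2: q = 0.1071 / 1.586 = 6.8%, so 130q = 8.8 cases; NPV = 1 − 9.6 / 213 = 95.5%.

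| r | q | PPV, answered | NPV, all visits | Sensitivity, all visits |
|---|---|---|---|---|
| 1 | 10.7% | 18.7% (goal missed) | 93.1% | 56% |
| 1.18 | 9.7% | 20.0% | 93.7% | 60% |
| 2 | 6.8% | 23.8% | 95.5% | 71% |
| 3 | 4.9% | 26.1% | 96.6% | 78% |
| 5 | 3.2% | 28.3% | 97.7% | 85% |
| 10 | 1.7% | 30.3% | 98.6% | 91% |

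With the planned 50% flagged instead of 54.9%, r = 1 gives PPV 20.4% and NPV over all visits of 93.3%. So both goals can be met in answered visits from about 93.3% (50% flagged) or 93.7% (site's own share) upward.

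**Break-even.** NPV over all visits is a weighted average of 99% in the screened-out visits and 1 − q in the unanswered ones, so it reaches 99% only if q is 1% or less, whatever the completion rate.

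**Higher completion.** At 80% answered and 50% flagged, r = 1 gives 1 − (0.8 × 0.5 × 0.01 + 0.2 × 0.107) / 0.6 = 95.8%.

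**The case against.** The restriction is disclosed: section 6a says plainly that the goals apply to patients with complete data. Completion is step 1 of the assessment, Column B of the enrollment report shows it by cluster, and missed eligibles are reviewed for appendicitis. Accuracy given an answered screen, reported beside a completion rate, is a legitimate quantity. Refining the questions would not by itself cure non-response. All of this stands. It does not settle which population the Hypothesis 1 conclusion covers, because the completion rate does not show how many cases lie in unanswered visits and the missed-eligible cases are not brought into the accuracy figures.

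A reader might infer that answering at the example site was driven by suspicion. The documents do not show this. The HP acknowledgment options include left-sided or epigastric pain, chronic pain and previous appendectomy, and the data dictionary in Appendix E describes that variable as the provider's acknowledgment of ineligibility. Some of these are in effect screen-negatives, and nothing says whether they were counted as unanswered (130) or screened out (83).

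A reader might also infer that the trigger's real NPV is 93-97%. The documents do not support that either. The 58.6% comes from one HP site in an example report, no KPNC completion rate is given, and the result turns on an unknown rate in unanswered visits. Selection also cuts both ways: the more strongly answering follows suspicion, the smaller the NPV shortfall. The 93.1% case at r = 1 misses the PPV goal with the site's own flagged share, so it is not an example of both goals being met.

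**Conclusion.** The mismatch between the population in Hypothesis 1 and the population analysed is real. As written, the hypothesis could be declared met for pediatric patients with abdominal pain on evidence from answered visits alone. Illustratively, with both goals met in answered visits, NPV over all visits is about 93-94% when answering is nearly unrelated to appendicitis, 95.5-96.6% at 2-3 times the rate, and 97.7-98.6% at 5-10 times. This rests on one site's completion, 10.7% appendicitis applying to those visits, NPV of 99% when answered, and an unanswered screen counting as not flagged. It is a scenario range and a reason to measure the value, not an estimate for the trial.

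The point bears on Aim 1 and on the refinement rule. The imaging comparisons in Hypotheses 2 and 3 do not depend on Hypothesis 1 being declared met.

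**What to change.** In section 6a (Hypothesis 1):

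1. Keep the complete-data NPV and PPV and the completion rate.
2. Add NPV, PPV and sensitivity over all potentially eligible visits: Column A of the enrollment report plus the HP visits where the triage alert did not fire, which Column A leaves out (5 at the example site). Count unanswered visits as not flagged, and take appendicitis status from the missed-eligible review already planned in section 9.
3. State that provider acknowledgments of ineligibility count as screen-negative. This affects the complete-data NPV and the completion rate; the all-visits NPV is the same either way, since neither group is flagged.
4. Report HP (nurse at triage, with provider fallback) and KPNC (provider in RISTRA) separately.
5. Word the Hypothesis 1 conclusion as holding *when the screening questions are answered*, unless the all-visits values also meet the goals.

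The cost is a change of SAP wording and one extra tabulation of data already planned. The downside is a less favourable reported NPV and sensitivity.
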